### Outcomes assessment, schedule, and procedures

The primary outcome of interest is comparing the load, a quantitative measure, of AMR genetic determinants in lower lid and rectal swab samples between arms A (SDD dose) and arm B (placebo) when corrected for baseline. The secondary outcome of interest is microbiome diversity of the ocular surface and gut through Shannon’s Index and Simpson’s index. Other exploratory outcomes include comparative analysis of (1) host conjunctiva inflammasome expression; (2) Ocular Surface Disease Index (OSDI), with scores ranging from 0 to 100 with higher scores indicating greater symptom severity; and (3) TBUT scores with numbers representing how many seconds after a full blink a discontinuity in the tear film appears. A normal tear breakup time is greater than 10 s of tear stability between blinks. All outcomes will be compared between the three study arms, corrected for baseline. Using R statistics tool, we will use ANOVA and chi-squared to measure aggregate quantitative and distributive qualitative values respectively in each arm and compare at the 4-week, 8-week, and 4-month mark. Both primary and secondary outcome analysis will emphasize differences noted at 4 months between study arms when corrected for baseline.

Participants will be seen for four approximately 40-min visits over the course of the study: at baseline, 4 weeks, 8 weeks, and once 4 months after their last dose of study medication. The four-week visit will be 25–35 days after the initial visit, the 8-week visit 49–63 days after the initial visit, and four months 90–150 days after the initial visit. Participants will undergo ocular evaluation at every visit as well as have a lower lid margin swabs from each eye and a rectal swab collected at baseline, 8 weeks, and 3 to 6 months after the first dose of study medication. Table 1 summarizes the procedure schedule for each visit under SPIRIT guidelines [9].

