## Methods

### Study design

The Ocular Rosacea microBiome Study (ORBS) is a three-armed, parallel, randomized, masked, placebo-controlled clinical trial. Participants with a diagnosis of symptomatic ocular rosacea (*n* = 50) at the University of California, San Francisco in San Francisco, California, United States, will be prospectively enrolled and randomized to one of three arms in a 2:2:1 fashion. (1) Arm A, a SDD dose of doxycycline (40 mg) taken for 8 weeks; (2) Arm B, an antibiotic dose of doxycycline (200 mg) taken for 8 weeks; and (3) Arm C, a placebo pill taken for 8 weeks. The trial will begin enrollment in December 2022. This protocol adheres to the Standard Protocol Items: Recommendations for Interventional Trials (SPIRIT) guidelines (Supplementary Table S1) and is registered on clinicaltrials.org (NCT05296837) [9]. This study was reviewed and approved by the Institutional Review Board at the University of California, San Francisco (21–34725) and will be done in accordance with the Declaration of Helsinki.

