### Intervention and sample size

The study coordinator will offer a sealed container to each participant during their primary visit. Each day’s dose will be marked in individual AM/PM packets. The coordinator will instruct the patients to take both doses, AM and PM, daily for 8 weeks. Participants taking 40 mg doxycycline will be taking one 20 mg doxycycline pill twice a day. Participants taking 200 mg doxycycline will be taking 100 mg twice a day. Participants allocated to placebo will be taking a placebo pill twice daily. The initial dose will not be offered under clinical observation as the pills for each study arm will look different and can unmask the participant to the study team. Participants will bring medication to all follow-up visits, compliance will be monitored by pill count performed by the study monitor. Monitoring for systemic side effects will be done at study follow-up visits via a questionnaire. We will not take objective measurements of adherence such as blood levels due to inefficiency and cost in this modest sample cohort.

We estimate that twenty patients per arm will provide over 80% power to detect a twofold increase in tetracycline resistance genetic determinants between Arms A and B, assuming the standard deviation in read number found previously, allowing for 10% dropout, and correcting for baseline [10]. As a secondary analysis, we estimate that twenty patients in Arm A and ten in Arm C will provide over 80% power to detect a three-fold increase in tetracycline resistance genetic determinants.

We estimate that twenty patients per arm will provide over 80% power to detect a difference between Arms A and B in Shannon’s diversity effective number of 2 (from an effective number of 10. That is, 10 to 8 or 10 to 12 effective number), assuming 10% drop-out and a standard deviation in the effective number of 1.9, found in two previous studies [11, 12]. As a sensitivity analysis, we anticipate similar power using Simpson’s diversity (again, expressed as an effective number).

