### Statistical considerations

The primary analysis for AMR outcomes will be ANOVA to compare determinants of resistance to doxycycline across the three study arms. Power estimates for a difference in the overall microbiome composition between Arms A and B (L1-norm PERMANOVA) are more difficult, but it is worth noting that a similar design found significant differences in the gut microbiome after oral azithromycin [11]. Individual organisms will be compared between arms using a Benjamin-Hochberg False Discovery Rate of 5%, with results considered exploratory. Both overall composition and individual species will be compared using stool and lower lid specimens. In addition, comparison of the host immune response in the lower lid between arms will be exploratory, as we do not have previous estimates of the necessary standard deviation. Although, note, this study will allow an estimate of that standard deviation for future studies.

All primary analyses will be intention-to-treat. Patients that do not attend their scheduled follow-up visits will be contacted by the study coordinator the following day via phone and offered rescheduling. Repeated attempts will be made weekly for 4 weeks to contact patients lost to follow-up. Patients who discontinue one of the study treatments due to intolerability or side effects will be observed until the end of the study period if willing to return.

An interim analysis for efficacy is not planned for this trial given a small sample size.

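### The primary outcome calls Arm B placebo, but Arm B is the 200 mg arm and placebo is Arm C, so the primary comparator, its size and its detectable effect are left ambiguous

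*Protocol article*

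**What the plan says.** All of the following is in the Protocol article.

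- **Study design** fixes the letters: "Arm A, a SDD dose of doxycycline (40 mg) taken for 8 weeks", "Arm B, an antibiotic dose of doxycycline (200 mg) taken for 8 weeks" and "Arm C, a placebo pill taken for 8 weeks". Fifty participants are allocated 2:2:1.
- **Intervention and sample size** keeps those letters. Twenty per arm are said to give over 80% power to "detect a twofold increase in tetracycline resistance genetic determinants between Arms A and B", allowing 10% dropout. Arm A against Arm C, at twenty against ten, is called a secondary analysis, with over 80% power for a threefold increase.
- **Outcomes assessment, schedule, and procedures** gives the primary comparison of resistance load as "between arms A (SDD dose) and arm B (placebo) when corrected for baseline". It then says that all outcomes will be compared between the three arms.
- **Statistical considerations** gives the primary resistance analysis as "ANOVA to compare determinants of resistance to doxycycline across the three study arms".
- **Introduction** sets the goal of learning whether 40 mg is truly sub-microbial, and hypothesizes that both doses raise resistance gene expression relative to placebo.

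**The concern.** The sentence that defines the primary outcome pairs a letter with a treatment that the letter does not denote. Either the letter or the word is wrong, and each correction gives a different trial result to report.

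The two contrasts answer different questions. A similar load under 40 mg and 200 mg could mean that both doses select for resistance or that neither does, and only the placebo arm separates these. A difference between 40 mg and 200 mg does not show that 40 mg leaves resistance unchanged. If the primary contrast stays unresolved until the data are unmasked, either one could be presented as primary with some textual support. The readings also differ in comparator size and in the effect the plan says it can detect.

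**Working it through.** **1. Arm sizes.** 50 split 2:2:1 gives 50 × 2/5 = 20, 50 × 2/5 = 20 and 50 × 1/5 = 10. This agrees with the twenty and ten in the sample size section. After 10% dropout: 18, 18 and 9.

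**2. The two readings side by side.**

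| | Letter B is right | Word placebo is right |
|---|---|---|
| Comparator | 200 mg (Arm B) | placebo (Arm C) |
| Sizes | 20 v 20 | 20 v 10 |
| Effect powered in the plan | twofold | threefold |
| Status in the sample size section | first power statement | secondary analysis |
| Other text in support | power for Shannon diversity is for A v B; the composition comparison (PERMANOVA) is discussed for A and B | goal and hypothesis in the Introduction |

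**3. Can the plan's own power figure be reproduced?** Not directly. The SD of the resistance measure is taken from a cited source and not printed, and no significance level is given. I assume a two-sided 5% t-test on the log2 scale, where twofold is a difference of 1. With noncentrality δ = difference / (SD × √(1/n1 + 1/n2)):

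- 18 v 18: √(1/18 + 1/18) = 0.333. Power of 80% needs a standardized difference of 0.961, so the claim of over 80% for twofold holds if the log2 SD is below 1/0.961 = 1.04.
- 18 v 9: √(1/18 + 1/9) = 0.408. Power of 80% needs a standardized difference of 1.190, so twofold against placebo needs a log2 SD of at most 1/1.190 = 0.84.

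**4. Twofold claim applied to placebo.** At SD 1.04, 18 v 9 gives δ = 1/(1.04 × 0.408) = 2.36 and power of about 62%. The fold detectable with 80% power is 2^(1.190/0.961) = 2.36.

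| Assumed log2 SD | A v B, twofold (18 v 18) | A v C, twofold (18 v 9) |
|---|---|---|
| 0.8 | 95% | 84% |
| 0.9 | 90% | 74% |
| 1.0 | 83% | 65% |
| 1.04 | 80% | 62% |

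**5. The plan's threefold claim for A v C.** Threefold is log2(3) = 1.585. At SD 1.04, δ = 1.585/(1.04 × 0.408) = 3.73 and power is about 95%. The two resistance power statements are therefore compatible with each other.

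**The case against.** The strongest reply is that this is one wrong word in one parenthesis. Study design and the sample size section agree on letters, sizes and contrasts. The plan never claims twofold power against placebo, and it already gives A v C its own figure at the right sizes. A reader might infer from the conflict that a power statement is wrong or that the trial is underpowered. The documents do not support that: the twofold claim can be neither confirmed nor refuted without the SD, and the threefold claim is compatible with it. The 62% is a worst case, taken at the largest SD consistent with the A v B claim; at a log2 SD of 0.84 or less there is no shortfall below 80%. This part of the objection stands.

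It is also fair that a three-arm ANOVA with a named pairwise contrast is a common structure, and that an analysis plan not shown here may explain how the two relate. The ANOVA sentence is weaker evidence than the label; it matters mainly because it does not resolve the label.

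A reader might further infer that SDD versus placebo was plainly the intended primary. The Introduction favours it, but the letter, the order of the power statements, the PERMANOVA text and the allocation, which gives 40 of 50 participants to A and B, favour 200 mg. That even division is why the one-word explanation does not dispose of the point: the rest of the article does not show which word is the slip.

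Masking does not explain it either. Randomization and masking uses A, B and C as masking letters, but Study design and the sample size section have already given them fixed meanings.

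**Conclusion.** The point holds as an internal contradiction in the definition of the primary comparison, and it must be fixed. The label in the outcomes section conflicts with Study design and the sample size section. The choice of reading changes the comparator (200 mg or placebo), its size (20 or 10) and the effect the plan says it can detect (twofold or threefold).

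The contradiction itself rests on the printed text alone. The power figures rest on assumptions: two-sided 5%, t-test on the log2 scale, 10% dropout in each arm, and an SD shown as a range. On those, power for twofold against placebo lies between about 62% and 84% for log2 SDs from 1.04 down to 0.8. They show only that the twofold claim belongs to A v B and should not be transferred to placebo without checking.

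**What to change.** Before unmasking:

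1. Correct the outcomes sentence so that letter and treatment match Study design.
2. Have the sponsor confirm which contrast was intended, name it as the single primary contrast, and use it in Intervention and sample size, in Outcomes assessment, schedule, and procedures, and in Statistical considerations. State there how it relates to the three-arm ANOVA. The stated goal and the placebo-referenced hypothesis make SDD versus placebo the better fit; that is a recommendation.
3. If placebo is primary, make the existing 20 v 10 threefold statement the primary power claim and do not carry the twofold claim over. Printing the assumed SD would let readers check it.
4. If 200 mg is primary, only the word placebo changes in the outcomes sentence and the stated power stands. The plan should then say that this contrast alone does not show whether 40 mg differs from placebo.

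The cost is a dated wording amendment. If placebo is chosen, the stated detectable effect for the primary contrast becomes less favourable, threefold in place of twofold.

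### The final assessment is timed three ways, and two of the timings exclude each other for anyone who completes 8 weeks of treatment

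*Protocol article*

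**What the plan says.** All the timing statements stand together under Outcomes assessment, schedule, and procedures in the Protocol article.

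- The visit list has four visits, the last of them "once 4 months after their last dose of study medication". The anchor for the last one is the end of dosing.
- The visit windows are then given in days. The final one is "four months 90–150 days after the initial visit", so the anchor is now the start of the study.
- The swabs have their own schedule, with "a rectal swab collected at baseline, 8 weeks, and 3 to 6 months after the first dose of study medication" and the lid swabs at the same times. The anchor is the first dose, and the range is wider.

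The same section says that the primary and secondary analyses will concentrate on between-arm differences at 4 months, corrected for baseline. It does not say from which anchor the 4 months are counted. It also plans to "compare at the 4-week, 8-week, and 4-month mark" for the outcomes in general.

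The length of treatment is set under Intervention and sample size: "The coordinator will instruct the patients to take both doses, AM and PM, daily for 8 weeks".

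**The concern.** The primary outcome is the load of resistance determinants in lid and rectal swabs, and the secondary outcome is microbiome diversity. Both are read mainly from the final sample, which is taken off drug. What that sample measures depends on how long the participant has been off drug: resistance one month after stopping and resistance four months after stopping are different quantities.

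The article's own Discussion treats persistence as relevant. It cites sequencing work in which resistance genes were still expanded three months after a short antibiotic course. Whether this trial looks before or after that point depends on which sentence the site follows. A swab taken at the wrong time cannot be retaken.

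**Working it through.** **Inputs**

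- Dosing: 8 weeks = 56 days (Intervention and sample size).
- Final visit, rule 1: 4 months from last dose.
- Final visit, rule 2: day 90 to 150 from the initial visit.
- Final swabs, rule 3: 3 to 6 months from first dose.
- 8-week visit: "the 8-week visit 49–63 days after the initial visit", used here as bounds on the day of the last dose.
- Assumptions: the first dose falls on or about the day of the initial visit, because the container is handed out then and the first dose is not observed; a month is 30.44 days, varied from 28 to 31.

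**Step 1. Reproduce the stated window.** Counting 4 months of 30 days from the initial visit gives day 120, and 120 ± 30 = 90 to 150 exactly. The window follows from the initial visit. It does not follow from the last dose.

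**Step 2. Put rule 1 on the same scale.** Visit day = last-dose day + 4 months.

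- Base case: 56 + 4 × 30.44 = about day 178.
- 30- and 31-day months: 56 + 120 = 176 and 56 + 124 = 180.
- 28-day months: 56 + 112 = 168.
- Most lenient case, last dose at day 49 with 28-day months: 49 + 112 = 161.

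Rule 2 closes at day 150. The gap is 178 − 150 = 28 days in the base case and 161 − 150 = 11 days in the most lenient case.

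**Step 3. Ask when both rules could be met.** Last-dose day ≤ 150 − 4 × 30.44 = about day 28 (day 30 with 30-day months, day 38 with 28-day months). Only someone who stopped treatment early could meet both.

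**Step 4. Place rule 3.** 3 × 30.44 = about day 91 and 6 × 30.44 = about day 183. This range contains nearly all of day 90 to 150 and also contains day 178. It conflicts with neither rule, but it runs about 33 days past the end of the visit window (183 − 150).

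**Step 5. Time off drug at the final sample, last dose at day 56.**

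| Rule followed | Study day | Days off drug |
|---|---|---|
| 1: last dose + 4 months | about 178 | about 122 |
| 2: day 90 to 150 | 90 to 150 | 90 − 56 = 34 to 150 − 56 = 94 |
| 3: 3 to 6 months from first dose | about 91 to 183 | about 35 to 127 |

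Rules 1 and 2 do not overlap. Even with the last dose at day 49, rule 2 reaches at most 150 − 49 = 101 days off drug, short of four 28-day months (112). Three months off drug (3 × 30.44 = 91 days) corresponds to day 56 + 91 = 147, so rule 2 reaches it only in its last few days, whereas rule 1 is always past it.

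**Step 6. The 4-week comparison.** Swabs are scheduled at baseline, 8 weeks and the final time point only. No resistance or diversity data exist at 4 weeks, so that comparison can apply only to outcomes measured then, such as OSDI and TBUT.

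**The case against.** The best defence is that a usable window exists. The only sentence that gives windows in days counts all three follow-up visits from the initial visit, the swab sentence also counts from the start of treatment, and 120 ± 30 reproduces the window exactly. On that reading, the reference to the last dose is a slip. This is plausible, but the article does not say so, and a site should not have to guess. Table 1 is not shown and may state an anchor. It could show which sentence was meant, but it could not make both true.

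A reader might infer more than the text supports, in four ways.

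- **That all three timings are incompatible.** They are not. The swab range overlaps each of the others; only the last-dose rule and the day 90 to 150 rule exclude each other.
- **That the estimate would be biased or meaningless.** All arms share one visit schedule, so an unclear or wide window mainly adds variance and blurs the estimand. It does not by itself distort the comparison between arms. The trial also runs at one institution, which may well follow a single working schedule.
- **That the loss of signal can be put in figures.** The documents give no rate at which a resistance signal fades, so any such figure would rest on an assumption from outside them.
- **That adjusting for days since last dose would repair it.** That variable arises after randomization and may depend on arm, for example through stopping for intolerability, so adjustment could itself introduce bias.

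The 4-week point is also small. The swab schedule is plain, and nobody could analyse samples that were not taken.

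**Conclusion.** The point holds as an internal contradiction at the time point the analysis emphasizes. Three different timings are given, and two are mutually exclusive for a participant who completes 8 weeks of treatment: about day 178 against a window that closes at day 150. The conflict survives every month length from 28 to 31 days and a last dose anywhere from day 49 to 63; the smallest gap is 11 days.

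The consequence is that time off drug at the key sample is either 34 to 94 days or about 122 days, so the comparison estimates either shorter or longer persistence of resistance. The size of any effect on the result cannot be derived from the documents. The result rests on a first dose at or near the initial visit and on full completion of dosing. It should be corrected before final visits begin because the primary and secondary outcomes depend on this sample; the 4-week wording is a minor matter alongside it.

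**What to change.** Before the first final visit, reconcile the three statements to one anchor (initial visit, first dose or last dose) and one window in days, used for both the final visit and its swabs. Say that the 4 months in the analysis sentence means this time point, and check that Table 1 agrees. The choice of anchor is the sponsor's and should follow from the persistence question the trial is meant to answer.

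As a minor edit, limit the 4-week comparison to outcomes measured at 4 weeks, such as OSDI and TBUT.

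The cost is wording in the protocol and, if needed, the visit schedule. No visits or samples are added, and the sample-size figures do not depend on this point.

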**Table 1 Tab1:**
[figure not shown]
SPIRIT schedule of planned ORBS trial procedures

The following ocular evaluation procedures should be performed in the order listed below to minimize disturbance of the ocular surface.Tear breakup time (TBUT)

It is preferable to get an automatic TBUT measurement, such as can be obtained through an Oculus keratography topographer. If this topographer is not available, then the TBUT should be measured by a physician masked to the study assignment. TBUT should be measured prior to application of anesthetic.

If in the case a doctor is measuring the TBUT, they should utilize the following procedure:
I.A fluorescein strip, only gently moistened, should be touched lightly to the tear meniscus.II.The patient instructed to blink several times.III.After even distribution of the fluorescein, the patient should be asked to blink again and then hold the eye open and the doctor starts a stopwatch.IV.The tear film is examined under cobalt blue light at the slit lamp.V.The doctor stops the stopwatch when the first break in the tear film occurs.VI.This measurement is repeated a total of three times, and all three times recorded.2)Intraocular pressure (IOP)

Non-contact tomography, such as iCare, is preferred as it requires no anesthetic that will alter the tear film. If iCare is not available, then traditional Goldmann applanation tonometry, as is routine with all eye examinations, may be performed at the end of the examination.3)Ocular Surface Disease Index (OSDI)

The patient will complete the standard 12-question questionnaire created by the Outcomes Research Group at Allergan Inc. (Supplementary S2).4)Ocular photography

Lid margin and conjunctiva will be photographed either with a slit lamp camera or with the ocular keratography topographer that has lid imaging modalities.

Sample collection procedures for the bilateral lower lid and rectum are summarized below. Study coordinators will provide separate sample collection kits for the lower lid and rectal samples. Samples will be processed in the Ralph & Sophie Heintz Laboratory at the Proctor Foundation for RNA deep sequencing with subsequent bioinformatic analysis.Bilateral lower lid swab collection

The study coordinator will obtain patient consent before collection. A sample collection tube labeled with the patient’s ID sticker will be filled with 1 ml of Zymo solution to stabilize the RNA/DNA in the sample. The collection kit will also contain an applicator swab, tube rack, and parafilm to prevent leakage after collection.

For sample collection, the physician will wear gloves and a mask, and instruct the patient that neither of them should speak during swabbing as RNA-seq is very sensitive and can pick up oral flora contamination in the air. No anesthetic drops will be used to further limit contamination. The physician will swab the first eye using the polyester tipped applicator swab (Fig. 2a), pulling down the lower eyelid and rolling the swab across the length of the inferior lid margin twice, while rotating the swab, and then repeating in the second eye. The order of eyes swabbed is inconsequential as both eyes will be swabbed with the same applicator. The physician will then open the sterile capped plastic tube container, place the swab tip down, and carefully snap the swab while holding the tube steady with the other (Fig. 2b). Immediately after capping the plastic tube, they will stretch the parafilm over the top for further leak protection (Fig. 2c) before placing the tube back on the rack.2)Rectal swab collection

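### The listed examination order puts the OSDI questionnaire after tear breakup time and tonometry without a reason, so when fallback methods are used the only ocular symptom score may follow contact with the eye

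*Protocol article*

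**What the plan says.** The ocular evaluation list follows Table 1 in the section on outcomes assessment, schedule and procedures. It opens with a rule on sequence: "The following ocular evaluation procedures should be performed in the order listed below to minimize disturbance of the ocular surface". The four items, in order, are TBUT, IOP, OSDI and photography.

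- **TBUT.** The preferred method is automatic: "It is preferable to get an automatic TBUT measurement, such as can be obtained through an Oculus keratography topographer". The fallback depends on equipment: "If this topographer is not available, then the TBUT should be measured by a physician masked to the study assignment". The physician's procedure begins with dye: "A fluorescein strip, only gently moistened, should be touched lightly to the tear meniscus". The patient then holds the eye open while the time to the first break is taken, three times in all.
- **IOP.** The preference reads: "Non-contact tomography, such as iCare, is preferred as it requires no anesthetic that will alter the tear film". If that device is not available, Goldmann applanation is allowed and may be left to the end of the examination.
- **OSDI.** "The patient will complete the standard 12-question questionnaire". The form itself is in Supplementary S2, which is not shown.

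The same section places the OSDI among the exploratory outcomes: "Ocular Surface Disease Index (OSDI), with scores ranging from 0 to 100 with higher scores indicating greater symptom severity". It also says that ocular evaluation takes place at every visit and that all outcomes are compared between the three arms with correction for baseline.

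**The concern.** The order exists to protect the ocular surface. That explains why a dye test or a tonometer should not precede a more delicate measurement. It does not explain why a paper questionnaire should wait behind either of them, since completing it first protects the surface equally well.

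Where the fallback methods are used, the patient may rate symptoms shortly after dye, timed measurements with the eye held open, or applanation. Because the method depends on which device is free, the handling before the questionnaire can differ between patients, and between one patient's baseline and follow-up. A switch of method would then enter the baseline-corrected score.

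At stake is the precision of the one ocular symptom measure named in the article. The only other patient questionnaire, under Intervention and sample size, concerns systemic side effects.

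**Working it through.** The plan gives no figure on this point, so there is none to reproduce. The check is to set the order against the device rules and see what can precede the OSDI.

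1. Automatic TBUT, then iCare: two examinations come before the OSDI, but as the protocol describes them there is no dye, anesthetic or contact.
2. Fluorescein TBUT, then iCare: dye and three held-open measurements come before the OSDI.
3. Either TBUT method, with Goldmann left to the end: tonometry comes after the OSDI.
4. Either TBUT method, with Goldmann in its listed second place: the wording permits deferral but does not require it, so applanation comes before the OSDI.

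Prior handling therefore ranges from none described (path 1, or path 3 with automatic TBUT) to fluorescein plus applanation (path 4 with the physician's TBUT). No statement ties a participant to one path across visits.

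**Illustration of size, on assumed inputs only.** Suppose prior fluorescein shifts the OSDI by d points, is used at a share p of visits, and is chosen independently at baseline and follow-up. Take simple change from baseline as the outcome. With 10% dropout, the planned 20, 20 and 10 patients become 18, 18 and 9. The chance difference between two arms then has SD

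d × √2 × √[p(1 − p)(1/n₁ + 1/n₂)].

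- p = 0.5, 18 v 9 (A v C): √[0.25 × (1/18 + 1/9)] = 0.204; × √2 = 0.29d.
- p = 0.5, 18 v 18 (A v B): √[0.25 × (2/18)] = 0.167; × √2 = 0.24d.
- p = 0.1, 18 v 9: √[0.09 × (1/18 + 1/9)] = 0.122; × √2 = 0.17d.
- One method kept throughout for each patient: 0.

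For d from 2 to 10 points, the p = 0.5 rows give about 0.6 to 2.9 points (A v C) and 0.5 to 2.4 points (A v B).

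This variation is unrelated to arm, so the more useful scale is how far it widens the standard error. At p = 0.5 it adds variance 2 × 0.25 × d² = 0.5d² per patient, and the standard error is multiplied by √(1 + 0.5d²/SD²). If the SD of OSDI change is 15 to 20 points (also assumed):

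- d = 2: √(1 + 2/400) to √(1 + 2/225), an increase of 0.2% to 0.4%.
- d = 5: √(1 + 12.5/400) to √(1 + 12.5/225), 1.6% to 2.7%.
- d = 10: √(1 + 50/400) to √(1 + 50/225), 6.1% to 10.6%.

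The share p = 0.5 gives the largest variance of any p, and the protocol's preference for the automatic method points to a lower one.

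**The case against.** The strongest reply is that this is a preference about questionnaire order with little behind it. The preferred methods involve no described contact, and Goldmann has an explicit route to the end of the visit. The order is the same in all arms, allocation is randomized, and patients and the physicians who measure TBUT are to be masked. The OSDI is exploratory, and the article gives power only for resistance determinants and diversity. Consistency of device within a patient is the kind of operational detail that an article may leave to the full protocol. Finally, momentary irritation matters only if the questionnaire picks it up; if its items ask about a past period, the shift would be small.

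Most of this stands, and it limits the point. Two stronger readings are tempting, and the documents support neither:

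- A reader might infer that the symptom score is always collected after the eye has been handled, to a degree that varies by visit. Path 1 in the check contradicts the first part. Variation between visits is permitted by the text, not planned.
- A reader might infer that a chance imbalance in fluorescein use could pass for a treatment effect. Method use unrelated to arm adds within-arm variance, which the standard error already reflects. It does not favor an arm or raise the false-positive rate.

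What the reply does not answer is the order itself. The article states the order together with its purpose, and that purpose gives no reason for the questionnaire to come third.

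**Conclusion.** The point holds as a minor, free improvement. The prescribed order places the OSDI after TBUT and IOP without need. When the fallback methods are used, the questionnaire may follow contact with the eye, and nothing shown keeps the method constant across a participant's visits. The result can be extra noise in an exploratory, baseline-corrected outcome. It is not systematic between-arm bias, and the primary resistance outcome and secondary diversity outcome do not depend on it.

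The size cannot be known from the documents. The illustration rests wholly on an assumed shift, an assumed share of fluorescein use, independence between visits and an assumed SD. Under those inputs the loss of precision is slight unless the shift is large, and it vanishes if each patient keeps one method.

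**What to change.** In the ocular evaluation list, put the OSDI first at every visit, before TBUT by either method, IOP and photography. Leave the relative order of the other three items unchanged, including the allowance for Goldmann at the end. Once the questionnaire comes first, the device used at that visit cannot affect it, so no rule on consistency of method is needed for the OSDI.

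The cost is one reordered line: the same questionnaire and visit length, and no added staff or procedure. The change is best made before enrolment begins, so that baseline and follow-up scores are collected in the same way.
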